## Abstract

**Background:**

In facioscapulohumeral dystrophy (FSHD) muscle function is impaired and declines over time. Currently there is no effective treatment available to slow down this decline. We have previously reported that loss of muscle strength contributes to chronic fatigue through a decreased level of physical activity, while fatigue and physical inactivity both determine loss of societal participation. To decrease chronic fatigue, two distinctly different therapeutic approaches can be proposed: aerobic exercise training (AET) to improve physical capacity and cognitive behavioural therapy (CBT) to stimulate an active life-style yet avoiding excessive physical strain. The primary aim of the FACTS-2-FSHD (acronym for Fitness And Cognitive behavioural TherapieS/for Fatigue and ACTivitieS in FSHD) trial is to study the effect of AET and CBT on the reduction of chronic fatigue as assessed with the Checklist Individual Strength subscale fatigue (CIS-fatigue) in patients with FSHD. Additionally, possible working mechanisms and the effects on various secondary outcome measures at all levels of the International Classification of Functioning, Disability and Health (ICF) are evaluated.

**Methods/Design:**

A multi-centre, assessor-blinded, randomized controlled trial is conducted. A sample of 75 FSHD patients with severe chronic fatigue (CIS-fatigue ≥ 35) will be recruited and randomized to one of three groups: (1) AET + usual care, (2) CBT + usual care or (3) usual care alone, which consists of no therapy at all or occasional (conventional) physical therapy. After an intervention period of 16 weeks and a follow-up of 3 months, the third (control) group will as yet be randomized to either AET or CBT (approximately 7 months after inclusion). Outcomes will be assessed at baseline, immediately post intervention and at 3 and 6 months follow up.

**Discussion:**

The FACTS-2-FSHD study is the first theory-based randomized clinical trial which evaluates the effect and the maintenance of effects of AET and CBT on the reduction of chronic fatigue in patients with FSHD. The interventions are based on a theoretical model of chronic fatigue in patients with FSHD. The study will provide a unique set of data with which the relationships between outcome measures at all levels of the ICF could be assessed.

**Trial registration:**

Dutch Trial Register, NTR1447.

## Background

Facioscapulohumeral dystrophy (FSHD) is the third most common inherited neuromuscular disorder. It is an autosomal dominant slowly progressive myopathy with a variable age of onset, mostly in the second or third decade of life. Its yearly incidence rate is approximately 1:20.000 [1]. The disease primarily affects the facial muscles, the muscles of the shoulder girdle (most typically the scapula stabilizers) and various leg muscles, while pelvic and trunk muscles are eventually affected as well [2-4]. The pattern of muscle weakness is often asymmetrical, and the rate and extent of progression may vary considerably with sudden periods of unexplained rapid disease progression. In a small percentage of the patients, even respiratory insufficiency may occur [5]. Only very recently, evidence became available that there may be a selective involvement of the central nervous system as well, in terms of decreased grey matter volume [6] and reduced intracortical inhibition [7]. Although FSHD is associated with a partial deletion of a critical number of repetitive elements (D4Z4) on chromosome 4q35, to date no causal gene has been identified and no curative treatment is available [3,8]. FSHD may eventually lead to serious disabilities of speech, swallowing, reaching, standing and walking, even in early adulthood. Twenty percent of the patients become wheelchair bound. Since no cure is available, rehabilitation is the mainstay of treatment [2,3,9].

Only recently it was shown by our group that severe fatigue, defined as a score equal or higher than 35 on the subscale fatigue of the Checklist Individual Strength (CIS-fatigue), was reported by 61% of the patients with FSHD. These severely fatigued patients had more problems with physical and social functioning as well as with mental and general health than similar patients without a severe fatigue. They also had more problems with concentration, initiating and planning [10]. As such, experienced fatigue should be clearly distinguished from muscle weakness, which is probably the most common and characteristic symptom of FSHD [11]. In a longitudinal study, we built a model of perpetuating factors for fatigue in patients with FSHD (figure 1). It appeared that lack of physical activity, sleep disturbances and pain all contributed to experienced fatigue. In addition, loss of muscle strength and pain contributed to fatigue through a lower level of physical activity. Ultimately, experienced fatigue and physical inactivity both contributed to the level of societal participation [12]. Thus, theoretically, in order to improve societal participation one should improve muscle strength, reduce pain, optimize physical activity and alleviate experienced fatigue. In addition, falling appears to be a major problem among FSHD patients. Our group was able to show that 65% of the patients reported falling at least once a year [13]. Since fall incidents often lead to fear of falling and avoidance behaviour, they have a serious negative impact on physical activity and participation.

**Figure 1 F1:**
[figure not shown]
**Model of perpetuating factors of experienced fatigue in patients with FSHD**.

Improving muscle strength by strength training and/or (anabolic) medication has shown not to be successful in patients with FSHD [14]. Until now, only one trial has investigated low-intensity aerobic exercises, indicating that aerobic training is a safe method to increase exercise performance [14,15]. Although, in general, physical activity does not appear harmful [16,17], more research is needed to establish whether AET is beneficial in patients with FSHD. Besides improving physical (aerobic) capacity, it seems important to optimize physical activity and change behaviour in daily life. Indeed, symptoms and signs of muscle weakness and fatigue as well as the anticipation of a (further) decline in physical capacity may elicit an inactive life-style, which may disproportionally affect physical activity, fatigue and societal participation. From this perspective, it might be beneficial to alter illness cognitions and coping styles by means of CBT. However, evidence for the effectiveness of CBT in patients FSHD is not yet available.

The primary objective of the FACTS-2-FSHD trial is:

- to study the efficacy of AET and CBT for decreasing chronic fatigue in patients with FSHD. It is hypothesized that both AET and CBT are more effective in decreasing fatigue than usual care, which is no therapy at all or occasional (conventional) physical therapy. The improvement by AET may be obtained through enhancement of physical (aerobic) capacity, whereas beneficial effects of CBT may be achieved through changes in daily activities and behaviour. By changing illness cognitions and improving coping style, the balance between actual behaviour and physical capacity will be optimized. Since changes achieved by CBT are more 'intrinsic', possible beneficial effects of CBT may last longer than those of AET.

Secondary objectives of the FACTS-2-FSHD trial are:

- to evaluate the effects of AET and CBT on bodily functions and structures as defined by the International Classification of Functioning, Disability and Health (ICF): lower extremity muscle strength, pain, psychological well being, cardiovascular risk factors, aerobic exercise tolerance, sleeping pattern, as well as biomarkers in blood and urine and structural and metabolic muscle tissue characteristics.

- to evaluate the effects of AET and CBT on the ICF level of activities: physical activity in daily life, self perceived functional status, and fall incidence.

- to evaluate the effects of AET and CBT on the ICF level of participation: limitations in participation and autonomy and quality of life.

- to evaluate the effects of AET and CBT on environmental and personal factors as defined by the ICF: coping style, illness cognitions, concentration problems, motivation, caregiver strain, experienced fatigue of the caregiver, social support and coping of the caregiver.

## Methods

### Study population

It is intended to include 75 FSHD patients, diagnosed on both clinical and genetic grounds, aged 18 years and older. All patients who participated in previous FSHD studies at the Radboud University Nijmegen Medical Centre [10,12,14,18] are approached by the primary investigator (NV). In addition, all patients known at the departments of Neurology and Rehabilitation of the Radboud University Nijmegen Medical Centre, University Medical Centre of Utrecht, Amsterdam University Medical Centre or any of the affiliated rehabilitation centres are invited to participate as well. In addition, patients who are registered in the Dutch neuromuscular "computer registry of all myopathies and polyneuropathies" (CRAMP) database [19] and/or who are member of the Dutch patient support organisation "vereniging spierziekten Nederland" (VSN) will be invited by the primary investigator (NV) and a member of the VSN, respectively, to take part in the study. If the patient is willing to participate, the primary investigator (NV) will check the inclusion and exclusion criteria (table 1) and estimate the disease severity using the Ricci score [20]. When a patient meets all the criteria, oral and written informed consent are obtained according to the declaration of Helsinki. Separate consent is asked to (i) obtain blood and urine samples, and/or (ii) undergo magnetic resonance imaging (MRI)/spectroscopy (MRS), and/or (iii) undergo muscle ultrasound. The study protocol was approved by the Dutch ethical committee CCMO (Centrale commissie mensgebonden onderzoek) and all participating centers granted (ethical) approval to participate.

**Table 1 T1:** Inclusion and exclusion criteria

Inclusion criteria
(1) age 18 years and older

(2) suffering from severe fatigue (CIS-fatigue ≥ 35) [21]

(3) ability to walk independently (ankle-foot orthoses and canes are accepted)

(4) being able to exercise on a bicycle ergometer

(5) being able to complete either type of intervention

**Exclusion criteria**

(1) cognitive impairment

(2) insufficient mastery of the Dutch language

(3) neurological or orthopedic co-morbidity interfering with the interventions or possibly influencing outcomes

(4) pregnancy

(5) use of psychotropic drugs (except simple sleeping medication)

(6) severe cardiopulmonary disease (chest pain, arrhythmia, pacemaker, cardiac surgery, severe exertional dyspnea, emphysema)

(7) epileptic seizures

(8) poorly regulated diabetes mellitus or hypertension

(9) clinical depression, as diagnosed with the Beck Depression Inventory for primary care (BDI-PC) [22,23]

### Randomization and blinding

Participants fulfilling all inclusion and exclusion criteria are randomised to one of three groups by creating computer-generated 'blocks' ensuring that the same number of participants is allocated to each group. Experimental group 1 (E1) receives AET and usual care for 3 times a week during 16 weeks. Experimental group 2 (E2) receives CBT and usual care once time a week during 16 weeks. Thereafter, both groups are followed up for 6 months. A third group (C) receives usual care only for 16 weeks and serves as a waiting list control group. After another 3-months follow-up (i.e. 7 months after inclusion), this group will as yet be randomised to either AET or CBT for 16 weeks and followed up until 6 months later (total time in study 17 months) (figure 2). All outcomes are assessed by blinded and independent physical therapists. At the beginning of each assessment, patients are always instructed not to reveal their group allocation to the blinded assessor.

**Figure 2 F2:**
[figure not shown]
**Study design T**.

### Interventions

#### Usual care

All participants receive usual care. In the Netherlands, patients with FSHD typically receive no therapy at all, or occasional (conventional) physical therapy. Patients are not restricted in any activities, but all co-interventions are monitored throughout the study by diaries and at every measurement.

#### Aerobic Exercise Training (AET)

The AET consists of aerobic cycling exercise on a bicycle ergometer. The training program has a duration of 16 weeks and comprises home training twice a week and a supervised training once a week. Training sessions consist of a 30-minute aerobic exercise period with a warming-up and cooling-down period of 5 and 3 minutes, respectively. The cardiovascular load during the training period is individually adjusted and increased from a level of 60% to 75% of the heart rate reserve (HRR). HRR is the difference between the predicted maximum heart rate and the measured resting heart rate. The HRR is equivalent to the difference between the maximum and resting maximal oxygen consumption (VO2max). Each participant is learned how to adjust the physical load to the preferred individual heart rate. Participants are supplied with a Monark 827E bicycle ergometer, a Garmin forerunner 50 heart rate watch with breast belt, and a log book with training instructions at home for the duration of the intervention. During each training, the heart rate is monitored continuously by the breast belt. The number of training sessions, the total time spent on AET, possible adverse effects and the training parameters (physical load, heart rate) are recorded in the individual log book. Once a week, individually supervised training is given by trained physical therapists during one-hour sessions in small groups in a nearby rehabilitation centre. During these sessions, therapy compliance in the home situation is verified by reading out the heart rate watches and checking the log books. In addition, instructions for the next week are provided. The (unblinded) primary investigator and physician (NV) gives instructions to the physical therapists and performs integrity checks at each treatment location.

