#### Cognitive Behavioural Therapy (CBT)

CBT will be focused on the perpetuating factors of fatigue as established in previous research [10,12,24] and based on experience in clinical practice. These factors encompass insufficient coping with the disease, dysfunctional illness cognitions, catastrophizing, deregulation of sleep, deregulation of activity, low social support and negative social interactions (see appendix 1 for the various modules). Because of large inter-individual differences, CBT will be adapted to the needs of each patient. For instance, barriers to become more physically active are explored and possibly alleviated in some patients, whereas overactivity is reduced in others. To determine which modules are appropriate, each perpetuating factor is assessed with specific tests, and within each module, the CBT approach is standardized (see appendix 1). The precise number of sessions is dependent on the number of modules. Each session has a duration of one hour and is given at the most nearby participating centre by a registered cognitive behavioural therapist, especially trained in CBT for FSHD. The therapists have been specifically trained to use the diagnostic tests and indicate the different modules and are regularly supervised by one of the investigators (GB).

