***ICF: environmental factors***	
Caregiver strain	Caregiver Strain Index of partner/caregiver (CSI) [41]
Experienced fatigue of patient	Checklist Individual Strength (CIS subscale fatigue, filled in by
from perspective of relative.	relative about patient) [21]
Experienced fatigue of partner.	Checklist Individual Strength (CIS subscale fatigue, filled in by relative about him/herself) [21]
Social support	Sociale steunlijst-subschaal discrepantie (SSL-D verkort) [42]
Coping of partner	Coping Inventory for Stressful Situations (CISS) [30]

*Measured only at inclusion. **Participants will be called weekly throughout the study by a telephone-computer to obtain fall incidence; in the case of fall incident(s), a subsequent telephone interview is held to obtain information about the cause and circumstances of falling, fall direction, possible injury and ability to get up from the floor. ***In all groups, three extra urine samples will be obtained at week 4, 8 and 12 of the intervention period.

At the level of bodily functions and structures, patients are asked to give separate consent for several 'invasive' assessments at baseline and after the intervention period. Blood and urine samples are collected by experienced nurses and will be explored by nuclear magnetic resonance (NMR) for possible biomarkers of disease and response to the interventions. Ultrasound measurements of the thigh muscles are made by an experienced ultrasound professional, blinded for the treatment allocation, and analyzed for muscle thickness and echo intensity. In addition, Magnetic Resonance Imaging (MRI) and ^31^P and proton (^1^H) Magnetic Resonance Spectroscopy (MRS) are performed by trained professionals, blinded for the assignment to the intervention. It has been shown that in vivo MRS is able to produce spectra of multiple metabolites simultaneously and is well suited to study energy metabolism in patients with muscular dystrophies [28,29]. The MR examinations start with T1 and T2 weighted images of the thigh for detailed structural analysis. Muscle involvement is specifically assessed by the presence of fatty infiltration on T1 weighted MR images. ^1^H MRS is used to assess muscle specific creatine as well as extramyocellular lipids and intramyocellular lipids levels, whereas ^31^P MRS is applied to get information about tissue pH and the level of high energy phosphates present in the different thigh muscles.

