#### Adverse events

An adverse event is defined as any undesirable experience or outcome. Specially assigned site investigators are instructed to report all adverse events immediately to the primary investigator (NV) and to evaluate each event for its date of onset, possible relation to the interventions (based on clinical judgment), possible treatment and course in time. In addition, adverse events can be reported by the participants directly to the primary investigator and physician (NV). All adverse events reported will be carefully monitored and registered until they have abated or a stable situation has been reached.

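### During the 16-week intervention only the AET group keeps a written record of possible adverse effects, so any between-group reading of non-fall adverse events would be open to ascertainment bias

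*Protocol article*

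**What the plan says.** **AET group.** Under Aerobic Exercise Training (AET), the 16-week programme "comprises home training twice a week and a supervised training once a week". Each participant has an individual log book at home for the duration of the intervention. Its contents are "The number of training sessions, the total time spent on AET, possible adverse effects and the training parameters". At the weekly supervised session, "therapy compliance in the home situation is verified by reading out the heart rate watches and checking the log books".

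**CBT group.** The section on Cognitive Behavioural Therapy describes one-hour sessions with a therapist and says "The precise number of sessions is dependent on the number of modules". The randomisation section gives the frequency as weekly for 16 weeks. No adverse-event record is described.

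**Usual care, which all groups receive.** Under Usual care, "all co-interventions are monitored throughout the study by diaries and at every measurement". The diaries are described for co-interventions, not for adverse events.

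**All groups.** The Adverse events section gives two routes. First, "Specially assigned site investigators are instructed to report all adverse events immediately to the primary investigator". Second, "adverse events can be reported by the participants directly to the primary investigator". Neither is described as a standard question at set times. For falls, the footnote to Table 2 says "Participants will be called weekly throughout the study by a telephone-computer to obtain fall incidence", and a reported fall leads to an interview that covers possible injury.

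**Use of the information.** The Discussion counts information on long-term adverse events among the strengths of the trial. Adverse events are not an outcome in Table 2. The Statistical Analysis section compares groups on the primary and secondary outcomes only.

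**The concern.** One group has a personal written prompt for adverse effects that a therapist looks at every week. The other two groups rely on someone volunteering or noticing an event. Minor events, such as muscle soreness or a few days of malaise, are the kind most likely to be written down in a training log and least likely to be volunteered without one. If the groups are then set side by side, AET may appear to cause more events than usual care or CBT when part of the difference is only that its events were more often recorded.

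The article gives readers reason to make that comparison. It notes that the earlier aerobic training study in this disease was uncontrolled and unblinded, with 8 patients, and it expects that a successful result could change guidelines on physical training. The control group is what would make the safety data more informative than that study, and unequal recording weakens this advantage. Blinding does not correct it either, because reports go to the primary investigator, whom the AET section describes as unblinded.

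**Working it through.** The article gives no adverse-event rate, safety power or safety test, so there is no stated figure to reproduce. The check compares the capture routes by group and then shows how far unequal capture could move a crude comparison.

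**Step 1. Apply one standard to all groups.** The standard is a general (non-fall) adverse-event record that the article states.

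| Route in the 16 weeks | AET | CBT | Usual care |
|---|---|---|---|
| Log book that includes adverse effects | yes | none stated | none stated |
| Weekly check of that log book | 1 × 16 = 16 | none stated | none stated |
| Reports by site investigators | yes | yes | yes |
| Reports by participants | yes | yes | yes |
| Weekly fall call | 16 | 16 | 16 |

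The log book spans 3 × 16 = 48 planned training sessions. The article lists what the book contains but states no prompt at each session, so 48 is a number of sessions, not of adverse-event enquiries. The stated purpose of the weekly check is compliance.

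**Step 2. Apply a looser standard: any scheduled contact.** Here no group is at zero. CBT has therapy sessions. Usual care has 16 weekly calls, urine samples at weeks 4, 8 and 12 (for those who consent), co-intervention diaries and the T1 visit. None of these is described as a general adverse-event enquiry. The groups differ in recording, not in whether participants are ever contacted.

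**Step 3. Illustrate the possible effect.** Let p be the true proportion with an event, equal in both groups, and let c be the probability that an event is captured.

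- Observed proportion = p × c
- Apparent risk ratio = (p × c_AET) / (p × c_control) = c_AET / c_control, so p cancels
- Apparent risk difference = p × (c_AET − c_control)

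All values of p and c are assumptions. The group size of 25 is from the Power section. With c_AET = 0.90:

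| c_control | Apparent risk ratio | Observed at p = 0.40 | Expected of 25 at p = 0.40 | Risk difference for p = 0.20 to 0.60 |
|---|---|---|---|---|
| 0.90 | 0.90/0.90 = 1.00 | 0.36 v 0.36 | 9.0 v 9.0 | 0 |
| 0.70 | 0.90/0.70 = 1.29 | 0.36 v 0.28 | 9.0 v 7.0 | 0.04 to 0.12 |
| 0.50 | 0.90/0.50 = 1.80 | 0.36 v 0.20 | 9.0 v 5.0 | 0.08 to 0.24 |

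The first row is the case in which the log book adds nothing. The article does not say which row is nearest the truth.

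**Step 4. Fix the period.** The log book is supplied only while the intervention runs. During follow-up the stated routes are the same in all groups, so the asymmetry is confined to the 16 weeks. If the same log book is used when waiting-list participants later receive AET, their before-and-after comparison has the same problem.

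**The case against.** The strongest reply has four parts.

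- **No such comparison is planned.** Adverse events are neither an objective nor a listed outcome, and the analysis section does not mention them. This stands. A reader might infer that the trial contains a biased safety comparison, but the article supports only that such a comparison, if made, would be open to bias.
- **The article is condensed.** The Adverse events section covers all groups, and a schedule of adverse-event questions could well be in the full protocol. This stands against any statement that usual-care participants are never asked. It does not remove the point, because the AET-only record is stated in the text. Even with a common schedule, that record could add events in one group unless they are kept apart.
- **Falls are already sought equally.** This stands. Falls are a major problem in this population according to the Background, and for falls and their injuries there is no asymmetry.
- **The long-term safety aim is hardly touched.** This also stands. The Discussion ties long-term events to the follow-up after the interventions, when the log book is no longer in use.

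Two stronger readings are tempting. One is that AET has 48 occasions to record an event, CBT up to 16 and usual care none. That counts log entries in one group and therapy contacts in another, while ignoring the contacts that usual care has. The other is that the bias is a risk ratio of 1.8. That is the extreme of an assumed range that starts at 1.00.

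**Conclusion.** The point holds in a limited form. As written, the plan records non-fall adverse events unequally during the 16-week intervention: AET has a dedicated record with a weekly check, while CBT and usual care have only the routes common to all groups. A crude comparison of those events would be open to ascertainment bias, probably against AET.

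The direction rests on the assumption that a written prompt raises capture. The size cannot be derived from the article. Under the assumed capture rates and equal true risk, the apparent risk ratio runs from 1.00 to 1.80. Fatigue outcomes, fall data and the described routes during follow-up are not affected. This is an inexpensive improvement to the safety information and does not call the design into question.

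**What to change.** 1. Ask one identical, standard adverse-event question in all three groups at contacts that already exist: T1, T2 and T3 and, if workable, the weekly telephone-computer call. T1 covers the period of the asymmetry. The comparison with usual care ends when the waiting-list group is re-randomised, about 7 months after inclusion.
2. Base any between-group summary of adverse events on the routes common to all groups: this question, the fall calls, and the reports by site investigators and participants. Events found by these existing routes should not be discarded.
3. List events known only from the AET log books separately, as descriptive information on training.
4. If the full protocol already has a common schedule of questions, only items 2 and 3 are needed.

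The cost is one more question and some additional follow-up of reported events. Because the article defines an adverse event very broadly, a weekly question could produce many reports. If that load is too great, asking at the shared visits alone is a reasonable minimum, at the price of longer recall.
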